### Intervention

2.4

As an intervention, we use the OurAir SQ 1750 Mobile Air Purification System for Virus-Free Air Indoors, engineered and customized by MANN+HUMMEL (Figure 2). The main filter stage is equipped with a high-efficiency nanofiber filter media, combining high separation efficiency (> 90% at 0.3 μm; equivalent to ePM_1_ 90% according to ISO 16890) with low differential pressure. The prefilter provides removal of coarse and fine particulate matter (e.g., dust, hair, pollen) and is additionally equipped with activated carbon layers selected for effective adsorption of VOCs (specified target gases: n-butane, toluene).

**Figure 2 fig2:**
[figure not shown]
Schematic overview of the OurAir SQ 1750 mobile air purification system.

Prior to the study, a simulation was performed to determine the optimal placement and operating point of the air purifier in the classroom. The optimum was defined as an air-cleaning rate corresponding to six air changes per hour (ACH). This 6-ACH target is applied by adjusting the device setting to the specific volume of each participating classroom. For the initial pilot study, however, the device was deliberately operated at the maximum airflow setting (1885.9 m^3^/h) to assess performance under worst-case conditions; this setting still resulted in a tolerable noise level (45.7 dB(A)).

To ensure effective blinding, the sham-intervention classroom has a mobile air purifier with the main filter and activated carbon prefilter removed. This device mirrors the operating noise of the functional units in the intervention classroom, neutralizing sound as a potential confounding variable (30).

## Exposure assessments

3

The indoor exposome (referring to the cumulative measure of external and internal exposures within the school environment) is characterized via screening questionnaires, indoor environmental monitoring, and biological monitoring.

### External exposure

3.1

#### Classroom and building characteristics and classroom activities

3.1.1

A screening questionnaire developed by the World Health Organization (WHO) (31), which addresses the structural and geographical characteristics of the school building and participating classrooms, is completed by the school’s responsible before the sampling campaign. The questionnaire examined (1) school building and classroom characteristics, (2) potential sources of indoor chemicals, and (3) other factors that affect IAQ (e.g., ventilation types and cleaning activities). More specifically, following questions are included: location and year of construction of the school; classroom orientation and dimension; type of surrounding environment (urban, suburban, rural), number of children and teachers (occupancy density), building heating system (electricity, fuel), building envelope (materials used to make floors, walls, windows, furniture), ventilation type (manual, mechanical, or hybrid), and visual inspection for mold, pests and dampness. Also, an overview of classroom activities during the sampling period, including the absence of children in the classroom (due to physical education) and the potential use of chemicals (e.g., painting), is provided through informal conversations with the head teacher of each participating class.

The data will be used to evaluate potential sources of indoor air pollutants and assess comparability between the classrooms participating in the study. The characteristics of school buildings, outdoor pollution sources, and the behavior of building occupants (activities in classrooms, cleaning routines, etc.) are expected to play a key role in understanding the IAQ of schools, as it depends strongly on the interaction between the building and the outdoor environment, and on the way the building is used, including the behavior of occupants (32).

#### Indoor environmental monitoring

3.1.2

The selection of indoor air pollutants investigated in this study takes into account the following factors: (1) Current list and wish list of priority substances included in a screening tool developed by the WHO for assessment of health risks from combined exposure to multiple chemicals in indoor air in public settings for children (33); (2) List of indoor air pollutants previously investigated in EU projects on IAQ in primary schools in Europe (e.g., SINPHONIE, InAirQ) (32, 34, 35); (3) Findings from a systematic review of human biomonitoring studies of children’s exposure to indoor air pollutants in school and home environments (25); (4) Other indoor pollutants investigated in European primary schools in peer-reviewed journals (36–39).

VOCs, aldehydes, polycyclic aromatic hydrocarbons (PAH), and particles are selected as target pollutant groups. Table 1 shows the individual target pollutants selected for indoor air measurements in the LEARN study. The current list of indoor pollutants is a provisional selection at this stage, and will be revised based on the results of subsequent measurement campaigns of LEARN. The study also selected IAQ-related microclimate parameters, as shown in Table 2, for measurement based on international standards such as the ISO 7726 (40) and the European standard EN 16798–1 (41), as well as the previous EU research projects (32, 34).

**Table 1 tab1:** List of pollutants selected for indoor air measurements in the LEARN study.

Selected air pollutants classified by chemical groups	
VOCs	Benzene
	Toluene
	Ethylbenzene
	o-Xylene
	m + p-Xylene
	Trichloroethylene
	Tetrachloroethylene
	Styrene
	1,4-dichlorobenzene
	Acetone
	Tetrachloromethane (Carbon tetrachloride)
	2-methylbutane
	n-butyl acetate
	n-decane
	1,2,3-trimethylbenzene
	Ethanol
	Acetonitrile
	2-methylpentane
	3-methylpentane
	Methyl cyclopentane
	2-methylhexane
	2,3-dimethylpentane
	3-methylhexane
	n-Heptane
	n-Hexane
	n-Pentane
VOCs (Terpenes)	Limonene
Aldehydes	Formaldehyde
	Acetaldehyde
	Acrolein
Particles	PM_2.5_
	PM_10_
	Ultrafine particles (UFPs)
	Black carbon (BC)
PAHs	Naphthalene (Naph)
	Benzo(a)pyrene (B[a]P)
	Phenanthrene (Phe)
	Benz[a]anthracene (B[a]A)
	Benzo[b]fluoranthene (B[b + j]F)
	Benzo[k]fluoranthene (B[k]F)
	Dibenz[a,h]anthracene (D[a,h]A)
	Indeno[1,2,3-cd]pyrene (Inp)
	Acenaphthene (Ace)
	Acenaphthylene (Acy)
	Anthracene (Ant)
	Benzo[g,h,i]perylene (B[ghi]P)
	Chrysene (Chry)
	Fluoranthene (Fln)
	Fluorene (Flu)
	Pyrene (Pyr)

**Table 2 tab2:** List of microclimate parameters selected for indoor measurements in the LEARN study.

Microclimate parameters
Carbon dioxide (ppm)
Indoor airflow velocity (m/s)
Relative Humidity (%RH)
Dry-bulb temperature (°C)
Natural wet-bulb temperature (°C)
Globe temperature (°C)

The environmental monitoring strategies of pollutants used in the LEARN study, including duration, period, and sampling location, parallel outdoor measurements, are developed mainly based on the methods recommended in the ISO 16000 series and the European standards for ambient air, as well as sampling methods adopted by WHO, NIOSH, previous EU projects, and peer-reviewed journals (32, 34, 42–44). There are two methods used to sample chemical pollutants: passive diffuse air sampling and active, pump-driven air sampling. An overview of all indoor (classroom) and outdoor sampling locations is shown in Figure 3.

**Figure 3 fig3:**
[figure not shown]
Overview of indoor (classrooms) and outdoor sampling settings in Belgium. **(a)** Placement of sampling devices inside the classroom and **(b)** at an outdoor location. **(c)** Detailed view of the devices: Passive samplers (red): Radiello diffusive samplers to measure VOCs (white, RAD130) and aldehyde (blue, RAD165) concentrations. Active samplers (yellow): Pumps connected with target-specific sorbent media. Microclimate monitor (blue): Testo 400 connected with the Wet Bulb Globe Temperature (WBGT) set. Air remediation (green): Mann+Hummel OurAir SQ 1750 Mobile Air Purification System. Particle sensors (purple): (1) TSI DustTrak™ DRX (Model 8,533) for simultaneous PM measurements, (2) Customized multi-sensor nodes for particle measurement, (3) AethLabs microAeth® (Model AE51) for black carbon (BC) measurement, (4) Naneos Partector for ultrafine particles (UFPs) measurement.

This environmental monitoring plan is primarily designed for and applied to the Belgian sites. When sampling campaigns are extended to the Danish and Greek sites, the plan will be adapted to local conditions. These adaptations are necessary to accommodate the variations in school schedules and specific spatial or logistical constraints in Denmark and Greece. However, to ensure comparability between countries, the key parameters and procedures across all monitoring sites will be standardized. Specifically, the target pollutants and parameters (Tables 1, 2) and the use of sampling approaches will be identical. In addition, all air samples collected from all sites will be transported to and analyzed by the laboratory at KU Leuven using standardized internationally recognized protocols.

Ideally, local site adaptations will be restricted to the physical placement of samplers and sampling times to align with local school hours. However, if specific samplings cannot eventually be performed at certain sites due to local logistical constraints, the pooled analyses will utilize only overlapping standardized environmental parameters collected from all sites. Any non-overlapping measurements will be analyzed independently as high-resolution datasets for specific sites to provide deeper mechanistic insights.

#### Active air sampling and analysis

3.1.3

Active air sampling is performed at one location in each classroom and one location outside the school building (e.g., playground, but under a protective roof) during school hours on regular school days throughout the week (2 days during BaP, 3 days during IP1 and IP2). Air samples are collected using an air sampling pump (1–5,000 mL/min) connected with corresponding sorbent tubes (for VOCs, aldehydes, and a gaseous fraction of PAHs) and PTFE filters (for a particulate fraction of PAHs), as visualized in Figure 4. VOCs are collected on activated charcoal tubes at a flow rate of 100 mL/min according to EN 14662–2; aldehydes on XAD-2 tubes coated with 2-(hydroxymethyl)piperidine (200 mL/min; NIOSH 2539); and PAHs on a combined assembly of PTFE filters and washed XAD-2 tubes (1,500 mL/min; NIOSH 5515). The air samples are then desorbed by solvent and analyzed by gas chromatography (GC), with flame ionization detection (FID) for VOCs and aldehydes, and with mass spectrometry (MS) for PAHs (45, 46).

**Figure 4 fig4:**
[figure not shown]
Schematic diagram of the setting of active air samplers for VOCs, aldehydes, and PAHs. It consists of a pump connected to a pollutant-specific sorbent tube. For VOCs, an activated charcoal tube is used at 100 mL/min. For aldehydes, a XAD-2 sorbent tube doped with 2-(hydroxymethyl) piperidine (2-HMP) is used at 200 mL/min. For PAHs, the setup includes a PTFE filter upstream of a washed XAD-2 sorbent tube at 1500 mL/min.

During the sampling campaign at each school, field blank samples and laboratory blank samples are collected to control contamination during transportation and sampling. All pumps used for active sampling are previously calibrated and verified after each sampling. After each sampling, the sorbent tubes and filters are capped and sealed in a clean, hermetically closed container and transported to the laboratory for refrigeration at −20 °C.

#### Passive air sampling and analysis

3.1.4

Passive air sampling is conducted over 5 days (from Monday morning to Friday afternoon). According to the ISO 16000-5 and ISO 16000-4 methods, respectively, using Radiello diffusive samplers (Figure 5; RAD130 for VOCs, RAD 165 for aldehydes) to collect air samples at three to four locations in each classroom and one location outside the school building (e.g., playground) (47). During the weekend of a specific “Intervention Period,” the cartridges are kept sealed in a clean glass tube from Friday after school hours until Monday morning when the school hours start again. For IP2, a new set of diffusive samplers is used. VOCs are determined by solvent desorption and GC-FID according to EN 14662–5. Aldehydes are determined by solvent desorption and high-performance liquid chromatography (HPLC) equipped with an ultraviolet (UV) absorption detector operating at 360 nm according to ISO 16000-4.

**Figure 5 fig5:**
[figure not shown]
Schematic diagram of a passive air sampling setup. (Left) The assembled Radiello diffusion sampler consists of a triangular support plate and a diffusive body. (Right) The cross-section shows the diffusion mechanism. The pollutant-specific adsorbent cartridge is placed inside the diffusive body. VOCs are sampled with RAD130 and analyzed according to EN 14662–5. Aldehydes are sampled with RAD165 and analyzed according to ISO 16000-4 (47).

During the sampling campaign at each school, duplicate samples are collected as internal quality control, while field blanks and laboratory blanks are collected to control contamination during transportation and sampling. All samples are sealed and refrigerated at −20 °C after sampling.

#### Microclimate monitoring

3.1.6

During IP1 and IP2, selected IAQ-related microclimate parameters, including carbon dioxide (CO₂) concentration (an indicator of ventilation rate), indoor airflow velocity, relative humidity, dry-bulb temperature, natural wet-bulb temperature, and globe temperature, are monitored continuously for five school days per week, alternating between R1 and R2 each week, as shown in Figure 6. The measurements are conducted using a universal IAQ instrument (model Testo 400, Testo SE & Co. KGaA) equipped with the IAQ and comfort kit (0563 0401) and the Wet-bulb Globe Temperature (WBGT) Kit (0618 7,220). All measurements are performed according to ISO 7726 standards. The WBGT index was calculated based on the ISO 7243 standard, which is a heat stress index and represents the thermal environment to which an individual is exposed.

**Figure 6 fig6:**
[figure not shown]
Schematic diagram of environmental monitoring.

### Biomonitoring of internal exposure

3.2

#### Blood sampling

3.2.1

Blood samples are collected from Belgian participants who have provided additional informed consent. To ensure standardized results, collection occurs between 12:00 and 14:00 on the final day of both BaP and IP1 (Figure 7). The blood samples will be analyzed for complete blood counts, BC detection, and specific health biomarkers. All samples will be archived and stored at the University Biobank Limburg (UBiLim). Country-specific protocol variations apply, as ethical and regulatory restrictions prevent blood collection in Denmark and Greece; blood-based biomonitoring data cannot be included in the pooled analysis of the entire three-country cohort. Therefore, analyses based on these specific biomarkers will be limited to the Belgian cohort, and these data will be used to validate external-to-internal exposure pathways for this specific cohort.

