### Sampling timeline

2.3

The LEARN study consists of four phases and takes approximately 6 to 7 weeks to complete for each school (Figure 1).

Baseline Period (BaP): No intervention is implemented at baseline (1 week).The participating classes are randomly assigned to one of two sequences in the crossover design: either starting with the intervention phase (installation of air purification units with filters) followed by the control phase (sham-intervention with installation of air purification units without filters)(R1), or vice versa (R2). Randomization is performed at the class level using computer-generated random numbers. The study is single-blinded, hence participants and teachers are unaware of the assignment of the intervention phase.Intervention Period 1 (IP1): The assigned (sham-) intervention is implemented and administered over 2 weeks.Washout Period (WP): A washout period of 1 to 2 weeks follows IP1, ensuring that the acute environmental and physiological effects of the initial intervention are fully diminished to maintain a true crossover design (26–29). Furthermore, this timeframe accommodates the academic calendar and classroom scheduling constraints. Potential carry-over effects will be further evaluated and adjusted for in the statistical analysis.Intervention Period 2 (IP2): The intervention status switches between the two groups, and the second phase of the study is conducted.

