### Skin microbiome

4.4

On the same days as blood collection, between 08:00 and 12:00 h, skin microbiome samples are collected using eNat® swabs (designed for nucleic acid collection and preservation) hydrated with 0.9% NaCl solution (Figure 7). These samples will be stored at UBiLim until further processing and analysis. Country-specific protocol variations apply, as ethical and regulatory restrictions prevent collection in Denmark and Greece.

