### Statistical strategy

5.3

Descriptive statistics will be used to summarize participant, classroom, and school characteristics; indoor air pollutant levels; microclimate parameters; biomarker concentrations; cognitive performance; and health outcomes.

To evaluate the impact of the intervention (vs. sham-intervention) and IAQ on longitudinal child outcomes, specifically cognitive performance and clinical/biological parameters (e.g., blood pressure), linear mixed-effects models will be applied. This model is specifically chosen to account for the longitudinal nature of the data, as multiple measurements will be collected from the same child. To handle the hierarchical clustering, random intercepts will be specified for school, class, and child. Background variables will be included as fixed-effect covariates in the models. Questionnaire data and clinical/pollution measurements will provide the necessary parameters to adjust for individual (e.g., socioeconomic factors and anthropometric measurements) and environmental (e.g., classroom pollution exposure, season) confounders, selected according to the requirements of each distinct analysis. Data collected from pre-sampling screening questionnaires will be used to adjust for building characteristics (e.g., building age, ventilation system) and external environmental factors (e.g., traffic exposure).

To analyze differences in environmental exposure levels (both external pollutants and internal exposure parameters) across different study phases (intervention vs. sham-intervention) and subgroups (e.g., schools), paired statistical tests (e.g., Student’s t-test, Mann–Whitney U test, or Wilcoxon signed-rank test) and ANOVA (or Kruskal-Wallis test, or Friedman test) will be used. The relationship between various parameters will be statistically analyzed using correlation and regression analysis.

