### Main strengths and weaknesses

6.2

The key strength of this study lies in its design. Comparing health outcomes, internal biomarkers, cognitive function, and well-being with IAQ before and after the application of a novel remediation strategy in a single-blinded crossover design allows for the precise determination of the effectiveness of the intervention. The crossover design also allows the same group of children to serve as their own controls, minimizing variability and providing a better understanding of the intervention’s health benefits. Due to the practical necessity of researchers installing the equipment, a single-blinded design was employed.

Another strength of this study is the carefully designed cognitive testing protocol. The potential for training effects was addressed by including two practice sessions during the BaP (57). Additionally, the use of standardized audio instructions ensures consistent delivery of test explanations across participants. Earlier studies often relied on oral explanations given by test administrators, which can introduce variability and potentially influence the results (65).

The same logic applies to the BP measurements. A baseline measurement is performed to allow children to become familiar with both the procedure and the researchers. During the BP assessments, five consecutive measurements are taken at each time point; the first two serve as internal acclimatization and will be excluded from the final analysis. This approach helps to minimize stress-related responses that can elevate BP readings during initial assessments (66). By addressing the acclimatization effect, the reliability of the blood pressure data is improved.

A third strength of this study is the modified standardized screening questionnaire with a scoring system. These questionnaires are given to and completed by the school staff responsible for each participating class. This enables easy identification of potential sources of indoor air pollutants in participating classrooms and ensures comparability between the two participating classrooms before the sampling campaign.

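### Blood and skin swabs are taken only at baseline and in the first period, so no child has a filter/sham pair, and the paired test planned for internal exposure cannot be computed for blood

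*Protocol article*

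**What the plan says.** **Sampling.** Section 3.2.1 (Blood sampling) covers Belgian children with additional consent: "collection occurs between 12:00 and 14:00 on the final day of both BaP and IP1". Section 4.4 (Skin microbiome), also Belgium only, ties swabs to those days: "On the same days as blood collection, between 08:00 and 12:00 h, skin microbiome samples are collected". Section 3.2.2 places urine collection in both IP1 and IP2, in Belgium and Denmark.

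**Conditions.** Section 2.3 (Sampling timeline) says of BaP: "No intervention is implemented at baseline (1 week". On allocation: "Randomization is performed at the class level using computer-generated random numbers". On IP2: "The intervention status switches between the two groups, and the second phase of the study is conducted".

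**Analysis.** Section 5.3 names "paired statistical tests (e.g., Student’s t-test, Mann–Whitney U test, or Wilcoxon signed-rank test" for exposure levels, described as "both external pollutants and internal exposure parameters) across different study phases (intervention vs. sham-intervention". Blood is not excepted, and blood sampling sits under Section 3.2, the heading for internal exposure.

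**Claimed strength.** Section 6.2 opens with "Comparing health outcomes, internal biomarkers, cognitive function, and well-being with IAQ before and after the application of a novel remediation strategy" in a crossover design. Section 4 lists the skin microbiome as a secondary outcome.

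**The concern.** A paired intervention-versus-sham test needs each child measured under both conditions. For blood, the stated schedule never produces that pair, so a test written into the plan has no data to run on.

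What remains within the child is the change from BaP to IP1. That change mixes the device with everything else that moved over the intervening weeks: weather, outdoor pollution, heating and window opening. In the filter-first sequence (R1) it could be mistaken for an intervention effect, and the before-and-after phrasing in Section 6.2 makes that easier.

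The randomised information on blood and skin is a parallel comparison of classes in one country. It is less precise than the crossover that readers will assume applies to every endpoint.

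**Working it through.** **1. What each child has under the stated schedule**

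| Endpoint | BaP (no device) | IP1 | IP2 | Filter/sham pair within child |
|---|---|---|---|---|
| Blood (Belgium) | yes | R1 filter, R2 sham | none | none |
| Skin swab (Belgium) | yes | R1 filter, R2 sham | none | none |
| Urine (Belgium, Denmark) | – | yes | yes | yes |

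BaP cannot stand in for sham, because the sham is a running unit without filters and BaP has no unit.

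**2. The protocol's own power figure (background)**

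Inputs from Section 2.2: residual SD 1; ICCs 0.05 (school), 0.10 (class), 0.50 (child); about 150 children per country; d = 0.5; two-sided 0.05; group × time contrast; random-effects meta-analysis; stated power 90%.

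Random intercepts cancel in a within-child change. With 75 children per sequence (assumed), SE per country = √[2·1²·(1/75 + 1/75)] = 0.231. Pooling three countries by DerSimonian-Laird in 200,000 simulated meta-analyses gives 91.0%, so the stated figure reproduces. This takes d in residual-SD units, with no between-site heterogeneity, no class-by-period variance and no dropout. It is a three-country figure; Section 3.2.1 takes blood out of pooled analysis.

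**3. Precision for blood, Belgium only, same assumptions**

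- Between sequences, BaP-to-IP1 change: variance = 2·(2/n + 2/n) = 8/n.
- Crossover, had IP1 and IP2 both been sampled: variance = 2/n.
- Variance ratio = 4, so SE ratio = 2 at any n.

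Power = Φ(0.5/SE − 1.96). The number consenting to blood is not given, so n is an assumed range:

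| n | SE, BaP/IP1 | Power | SE, IP1/IP2 | Power |
|---|---|---|---|---|
| 150 | 0.231 | 58% | 0.115 | 99% |
| 100 | 0.283 | 42% | 0.141 | 94% |
| 75 | 0.327 | 33% | 0.163 | 86% |
| 50 | 0.400 | 24% | 0.200 | 71% |

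**4. Class as the unit, with baseline adjustment**

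Total variance = 1/0.35 = 2.857, giving school 0.143, class 0.286 and child 1.429. For an assumed 8 classes of 19 (4 per sequence):

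- Class-mean variance = 0.143 + 0.286 + (1.429 + 1)/19 = 0.556.
- Correlation of BaP and IP1 class means = (0.143 + 0.286 + 1.429/19)/0.556 = 0.905.
- Residual variance after adjustment = 0.556·(1 − 0.905²) ≈ 0.100.
- SE = √(0.100·2/4) = 0.224, against crossover SE = √[(2/19)/8] = 0.115.
- Detectable effect at 80% power, (t.975 + t.80)·SE with 5 and 6 df: 3.490·0.224 = 0.78 against 3.353·0.1147 = 0.38 residual SD.

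The same formulas under other assumed layouts (df = classes − 3 and classes − 2):

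| Classes × children | SE, adjusted parallel | SE, crossover | Ratio | Detectable effect, parallel / crossover |
|---|---|---|---|---|
| 6 × 25 | 0.227 | 0.115 | 1.96 | 0.94 / 0.43 |
| 8 × 19 | 0.224 | 0.115 | 1.95 | 0.78 / 0.38 |
| 10 × 15 | 0.224 | 0.115 | 1.94 | 0.73 / 0.37 |
| 8 × 10 | 0.304 | 0.158 | 1.92 | 1.06 / 0.53 |

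The detectable effects move with the layout; the ratio stays close to 2. Class-by-period variance would widen every entry.

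**The case against.** Several counter-arguments have force and limit the point.

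- **Urine.** A reader might infer that the paired plan fails for internal exposure as a whole. It does not: urine is collected in both periods, so the sentence in Section 5.3 works there. This stands; the conflict is confined to blood markers.
- **Microbiome.** A reader might infer that the paired-test sentence also covers the microbiome. That sentence concerns exposure levels, while the microbiome is a secondary health outcome and would fall, if anywhere in Section 5.3, under the mixed models. This stands; only the sampling gap is shared.
- **A menu of tests.** The list is given by way of example, and it includes the unpaired Mann–Whitney test and ANOVA. True, but the text introduces the list as paired, and nothing assigns an unpaired test to blood.
- **Stated use of blood.** Section 3.2.1 says that blood serves to validate exposure pathways, which needs no filter/sham pair. This softens the conflict without exempting blood from Section 5.3.
- **Usable data.** The mixed model in Section 5.3 can estimate an R1-versus-R2 difference in change, with sham as the concurrent control. This stands: the data are not lost.
- **Own-control wording.** The own-control sentence in Section 6.2 refers to health benefits and names no blood marker. This also stands. What fails for blood is the adjacent sentence, which places internal biomarkers within the crossover comparison.
- **Overstated power and misuse.** A reader might infer that the protocol overstates its power for blood, or plans an R1-only before-after analysis. It does neither: no power is given for blood, and no such analysis is written down.

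None of this supplies the missing pair.

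**Conclusion.** The point holds in a narrow form. As scheduled, no child has both a filter and a sham sample of blood or skin. The paired intervention-versus-sham test in Section 5.3 cannot be computed for blood markers, and the crossover strength that Section 6.2 claims for internal biomarkers does not extend to blood. This is a conflict between stated passages, not a detail left to an analysis plan.

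The within-child change from BaP to IP1 confounds device with time. The only randomised contrast is between sequences, by class, in Belgium, with an SE about twice that of a crossover at equal n. That ratio is stable over the layouts tried. The power and detectable-effect figures are illustrations, because they rest on assumed class numbers and consent, on the Section 2.2 variance components applying to blood and skin, and on no class-by-period variance.

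The endpoints are not primary. The correction should be made, but the main crossover analyses of cognition and blood pressure are untouched. Figure 7 is not shown, but the text of Sections 3.2.1 and 4.4 is explicit.

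**What to change.** Reconcile Sections 3.2.1, 4.4, 5.3 and 6.2.

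- **Section 5.3:** limit paired intervention-versus-sham tests to endpoints sampled in both IP1 and IP2. For blood and microbiome, compare R1 with R2 at IP1, adjusted for the BaP value and allowing for clustering by class. State that a BaP-to-IP1 change within one sequence is not evidence of an intervention effect.
- **Section 6.2:** confine the crossover and own-control claim to outcomes measured in both periods.
- **Alternative:** if IP2 blood and swabs are in fact collected, correct the sampling text in Sections 3.2.1 and 4.4 instead.

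The first route needs wording and a model specification but no new samples. Its cost is that precision for these non-primary endpoints will be visibly less favourable than a crossover would give.
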